## Abstract

**Background:**

Herpes zoster (HZ) patients often experience herpes zoster-associated pain (ZAP). Thoracic paravertebral nerve block has been proven effective in relieving ZAP and reducing the incidence of postherpetic neuralgia (PHN). Compared to dexamethasone, dexamethasone palmitate (DXP) has stronger anti-inflammatory effects, a longer duration of action, and fewer adverse reactions. This study evaluates the efficacy and safety of ultrasound-guided thoracic paravertebral injection of DXP combined with ropivacaine for treating thoracic ZAP, compared to traditional famciclovir therapy.

**Methods:**

This prospective, randomized, controlled, open-label, endpoint-blinded, single-center trial will recruit 254 patients with ZAP. Patients will be randomly assigned in a 1:1 ratio to the intervention group (thoracic paravertebral injections of DXP combined with ropivacaine and antiviral therapy) or the control group (antiviral therapy). Assessments will include pain intensity, quality of life, sleep quality, inflammatory markers, and adverse events.

**Ethics and registration:**

This study strictly adheres to the 2013 SPIRIT Statement and the Declaration of Helsinki and has been approved by the Ethics Committee of the Second Affiliated Hospital of Guangxi Medical University (Approval Number: 2024-KY(0505)). This clinical trial is registered on the Chinese Clinical Trial Registry platform (ChiCTR) at https://www.chictr.org.cn/index.html (ChiCTR2400087273), registered on 2024-07-24. The results will be disseminated through scientific journals and conferences, aiming to provide evidence supporting the global management of ZAP. The study is expected to start on 1 August 2024, and continue until 31 July 2027.

## Introduction

In adults, the reactivation of varicella-zoster virus (VZV), which lies dormant in the dorsal root or trigeminal ganglia, typically results in herpes zoster (HZ). This condition is more common in individuals over the age of 50 (Sun et al., 2021; Cohen, 2013). Due to the neural damage and acute neuritis caused by VZV, patients experience persistent and severe pain, referred to as herpes zoster-associated pain (ZAP), which can become severe during the acute phase of the disease and often progresses to postherpetic neuralgia (PHN) if it persists beyond 90 days, posing significant treatment challenges (Ahronowitz and Fox, 2018; Ma et al., 2022; Rowbotham and Petersen, 2001).

Despite the widespread use of antiviral agents, anticonvulsants, antidepressants, and opioid analgesics, a subset of patients may still require additional therapeutic interventions to achieve adequate symptom control (Patil et al., 2022). This is particularly pertinent for individuals presenting with higher initial pain scores, advanced age, or comorbid conditions, as they remain at an elevated risk for developing PHN (Hashizume et al., 2022; Zhou et al., 2021; Wang et al., 2019). PHN significantly impacts patients' daily lives, leading to anxiety, depression, and sleep disturbances, making the prevention of PHN crucial for HZ patients (Wang et al., 2019). The side effects of medications, such as dizziness and drowsiness from gabapentin or pregabalin, and gastrointestinal issues from opioids, further complicate management strategies (Wang et al., 2023). Therefore, it is essential to minimize ZAP and prevent the occurrence of PHN.

Neuropathic pain is characterized by alterations in ion channels, activation of immune cells, and the involvement of neuroglial mediators. Among the commonly used medications, sodium channel blockers play a crucial role in managing this condition (Wang et al., 2021a). Ropivacaine, a potent sodium channel blocker, achieves its analgesic effect by reversibly inhibiting sodium ion influx, thereby blocking nerve impulse conduction. It is noted for its prolonged duration of action compared to lidocaine and is widely recognized for its safety due to its lipophilic properties, which confer reduced toxicity to both the cardiovascular and central nervous systems (Kaufman et al., 2005). A 0.2% concentration of ropivacaine is effective in providing analgesia with minimal motor impairment, making it suitable for epidural analgesia (Dresner et al., 2000).

Corticosteroids are frequently employed for postoperative pain relief in various surgical procedures, yielding favorable outcomes (Bai et al., 2020). Dexamethasone, a potent corticosteroid with an extended duration of action, has been demonstrated to provide effective adjunctive analgesia in procedures such as total knee arthroplasty (El-Boghdadly et al., 2021) and tonsillectomy (Basuni et al., 2013), as well as prolonging the duration of nerve blocks (Hauritz et al., 2018). It is commonly used as an adjunct for pain relief (Chong et al., 2017). Intrathecal steroid injections or nerve blocks are methods for effectively preventing and treating PHN (Wang et al., 2009). Ultrasound-guided thoracic paravertebral block (TPVB) is effective for ZAP and reducing the incidence of PHN (Ma et al., 2022; Abdelwahab et al., 2022; Deng et al., 2023; Kim et al., 2017).

Dexamethasone palmitate (DXP) is a liposomal formulation of dexamethasone, which exhibits superior anti-inflammatory efficacy, prolonged action, and reduced side effects (Lorscheider et al., 2019). DXP has been effectively utilized for pain management in conditions such as musculoskeletal disorders (Lee et al., 2022), rheumatoid arthritis (Lorscheider et al., 2019), and in video-assisted thoracoscopic surgery (Hui et al., 2023). While particulate steroids in epidural injections have been implicated in postoperative embolic events (Malhotra et al., 2009), mixing ropivacaine with dexamethasone sodium phosphate does not result in significant particulate formation, thereby enhancing safety (Wang et al., 2021b). Consequently, the combination of DXP and ropivacaine is considered both safe and effective.

A previous prospective study involving 10 patients with ZAP demonstrated the safety and efficacy of thoracic paravertebral injections of a single low-dose mixture of DXP combined with ropivacaine. However, this study was constrained by a limited range of outcome measures and the absence of long-term follow-up, hindering a comprehensive assessment of the long-term safety and efficacy of this therapeutic approach (Pu et al., 2022).

To rigorously evaluate the effectiveness of DXP combined with ropivacaine in treating ZAP and preventing PHN, a larger-scale, prospective, randomized, single-center study is warranted. Given the prolonged duration of action of ropivacaine and the enhanced anti-inflammatory efficacy, extended duration, and reduced side effects of DXP (Lorscheider et al., 2019), we hypothesize that a single injection of DXP combined with ropivacaine will reduce the incidence of PHN and effectively alleviate ZAP. Only patients whose NRS-11 score remains ≥4 after 2 weeks of intervention will receive an additional ultrasound-guided thoracic paravertebral injection.

### Objectives

The primary objective of this trial is to compare the efficacy of DXP combined with ropivacaine versus antiviral treatment alone in preventing ZAP from progressing to PHN within 12 months of follow-up, with the primary evaluation metric being the incidence rate of PHN, defined as a Numeric Rating Scale (NRS-11) score of ≥4 3 months after rash onset.

Secondary objectives include assessing the reduction in pain intensity, improvement in sleep quality (using the Pittsburgh Sleep Quality Index), enhancement of quality of life (using the Short Form Health Survey SF-12), decrease in weekly analgesic consumption, and changes in levels of inflammatory markers (C-Reactive Protein (CRP), Tumor Necrosis Factor-alpha (TNF-α), and Interleukin-6 (IL-6)).

## Methods

### Patient and public participation

Patients and/or the public did not participate in any stage of the design, execution, reporting, or distribution of the plans of this study.

### Study design and participants

This study is a prospective, randomized, open-label, endpoint-blind, single-center trial. The trial aims to recruit 254 patients with ZAP from the Second Affiliated Hospital of Guangxi Medical University. Participants will be randomly assigned in a 1:1 ratio to the intervention group or the control group. The intervention group will receive DXP with ropivacaine via thoracic paravertebral injection in addition to antiviral therapy, while the control group will receive antiviral therapy alone.

Before the study begins, all researchers will undergo standardized training covering the trial content, treatment strategies, methods, evaluation, and quality control, and they must pass an assessment. All patients will undergo a detailed explanation and informed consent process before enrollment and will receive comprehensive evaluations at baseline and during follow-up, including assessments of pain intensity, quality of life, sleep quality, and adverse events. The patient flowchart of this study is shown in Figure 1. This protocol conforms to the Standard Protocol Items: Recommendations for Interventional Trials checklist (Chan et al., 2013).

**FIGURE 1 F1:**
[figure not shown]
Trials flow diagram of the trial.

### Inclusion criteria

(1) Age ≥50 years with a diagnosis of thoracic HZ.(2) Disease duration ≤2 weeks.(3) Baseline pain intensity with an NRS-11 ≥ 4 points (Baseline pain intensity is the mean pain intensity score within 24 h before randomization).(4) Patients experiencing a first episode of HZ who have not received any other interventions.

### Exclusion criteria

(1) Special types of HZ infection: Patients with disseminated HZ or HZ at other locations.(2) Puncture risks: Patients with systemic infections, coagulation dysfunction, ongoing anticoagulant/antiplatelet therapy, infections at the puncture site, or thoracic spine abnormalities affecting ultrasound guidance.(3) Special populations: Pregnant or lactating women, individuals with immunodeficiency, severe cardiovascular, cerebrovascular, respiratory diseases, or other serious systemic conditions that impede treatment cooperation, and patients with mental illness.(4) Medication allergies: Patients with allergies to treatment-related drugs (e.g., steroid medications, famciclovir, gabapentin, pregabalin, Nonsteroidal Anti-Inflammatory Drugs (NSAIDs), tramadol) or contraindications for nerve block therapy.

### Withdrawal criteria

(1) Health Changes: Participants developing additional health issues, complications, or significant physiological changes that render them unsuitable for continued participation will be classified as dropouts.(2) Adverse Events: Participants experiencing serious or critical adverse events, which, upon our research team’s assessment, necessitate discontinuation, will be withdrawn from the study.(3) Protocol Violations: Participants who self-administer non-protocol drugs or undergo external treatments will be considered in breach of the protocol and will be excluded.(4) Voluntary Withdrawal: Participants may opt to withdraw for personal reasons or may be lost to follow-up during the concluding phase of the study.

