#### Blinding method

Due to the nature of the interventions (nerve block vs oral antiviral medication), blinding of patients and treating physicians is not feasible. However, all medication packaging will be standardized by an independent pharmacy service to minimize bias related to treatment allocation guessing. Endpoint assessments for efficacy and safety will be conducted by a dedicated team of clinicians who are blinded to treatment allocation. This team will not be involved in the daily management of the participants.

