#### Intervention group

Patients in the intervention group will receive the same antiviral therapy as the control group. Additionally, they will undergo ultrasound-guided thoracic paravertebral injections. If the patient’s NRS-11 score remains ≥4 2 weeks after the initial intervention, they will receive an additional ultrasound-guided thoracic paravertebral injection. A 5 mL mixture consisting of 0.2% ropivacaine and 4 mg DXP will be injected at each thoracic paravertebral site corresponding to the affected nerves.

We adopted an ultrasound-guided approach for thoracic paravertebral nerve block, as detailed in Pu et al. (2022). The procedure involves a four-step confirmation of the thoracic segment, followed by an in-plane puncture technique. The midpoint of the thoracic inferior articular process and parietal pleura serves as the puncture endpoint. Real-time ultrasound imaging facilitates the accurate placement of the needle tip. A mixture of local anesthetics and corticosteroids is administered for effective neuropathic pain management.

All patients will receive standard pain management, including anticonvulsants, antidepressants, or opioid analgesics, if their NRS-11 score remains ≥4 after treatment (Valladales-Restrepo et al., 2023).

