#### Primary outcome

Incidence Rate of PHN: PHN is defined as a condition characterized by pain in the dermatomal area that persists for a duration exceeding 3 months following the resolution of the herpetic rash (Kost and Straus, 1996). The incidence rate of PHN will be precisely determined by assessing the percentage of patients who exhibit an NRS-11 score ≥4 during scheduled follow-up visits at 3, 6, and 12 months (patient-reported).

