### Sample size calculation

Based on previous research data, the incidence of PHN in patients over 50 years old who receive standard antiviral treatment for HZ is 34.8%, while the incidence of PHN after repeated TPVB injections with lidocaine and triamcinolone is 16.3% (Ma et al., 2022). We predict a similar incidence rate in this study, based on the comparable treatment regimen and patient population. Sample size calculation is performed using PASS V.15 software (NCSS, Kaysville, UT, United States) with α = 0.05, β = 0.1, and power = 90%. Considering a dropout rate of 10%, we plan to recruit 127 patients per group, totaling 254 patients, with a 1:1 randomization ratio.

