### Handling bias and missing data

Multiple imputation will be used to address missing data. For outliers, the decision to correct, remove, or apply data transformation methods will be based on the source and nature of the outliers to mitigate their impact. We will conduct sensitivity analyses to assess the impact of missing data. Potential sources of bias will be addressed through thorough data monitoring and regular audits by the DMC.

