### Statistical analysis

Data analysis will be conducted using R 4.3.0 software. Both intention-to-treat (ITT) and per-protocol (PP) analyses will be performed. The ITT analysis will include all randomized participants, regardless of adherence to the protocol, to avoid bias from excluding participants who may have dropped out or not followed the protocol precisely. The PP analysis will only include participants who completed the study according to the protocol, providing a measure of efficacy under ideal conditions. This dual approach ensures the robustness and generalizability of the results. The statistical methods for primary and secondary outcomes are as follows.

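### Withdrawal criterion 3 excludes patients who use outside treatment without limiting this to the per-protocol set, so the primary pain outcome may go uncollected for patients whom the ITT analysis must include

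*Protocol article*

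**What the plan says.** The Withdrawal criteria section of the protocol article lists four grounds. Item 3 reads: "Participants who self-administer non-protocol drugs or undergo external treatments will be considered in breach of the protocol and will be excluded". Nothing there or elsewhere restricts this to an analysis set, and nothing says whether assessments continue after a breach.

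The Statistical analysis section plans two analyses without ranking them. On the first: "The ITT analysis will include all randomized participants, regardless of adherence to the protocol". The stated reason is to avoid the bias that comes from leaving out people who dropped out or did not follow the protocol. On the second: "The PP analysis will only include participants who completed the study according to the protocol".

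Handling bias and missing data states: "Multiple imputation will be used to address missing data". It adds sensitivity analyses for the impact of missing data.

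Three other places matter:
- The Primary outcome section bases PHN on a patient-reported NRS-11 of 4 or more at the 3-, 6- and 12-month visits. Study outcomes names month 3 as a primary time point.
- The Blinding method section concedes that "blinding of patients and treating physicians is not feasible".
- The Intervention group section provides pain treatment in both arms: "All patients will receive standard pain management, including anticonvulsants, antidepressants, or opioid analgesics, if their NRS-11 score remains ≥4 after treatment".

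**The concern.** Criterion 3 acts on the same kind of non-adherence that the ITT definition says must not matter. If exclusion ends follow-up, the ITT analysis still counts the patient but has no outcome for anyone who breached before month 3. For a later breach the month-3 value is on record, but the remaining visits are lost.

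The reason for the loss is what makes this more than a wording slip. People look for outside treatment when pain persists, and the endpoint is pain. Patients know their arm, and controls know that they had no block. Exclusion could therefore depend on the coming outcome and differ between arms. This is an inference; the protocol does not state it. If it is right, the PHN rates and relative risk are distorted, and no later analysis plan can recover scores that were never collected.

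**Working it through.** **The plan's own figure.** Inputs from Sample size calculation: control PHN 34.8%, intervention 16.3%, α = 0.05 (taken as two-sided, which reproduces the result), power 90%, dropout 10%.

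n = [1.960·√(2·p̄·(1−p̄)) + 1.282·√(p₁(1−p₁) + p₂(1−p₂))]² / (p₁−p₂)², with p̄ = (0.348 + 0.163)/2 = 0.2555

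= [1.960·√0.3804 + 1.282·√0.3633]² / 0.185² = 114.7, so 115 per group.

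115 × 1.1 = 126.5, so 127; 115/0.9 = 127.8, so 128. The stated 127 is reproduced. Power is 92.7% with 127 per arm analysed and 89.8% with 114 per arm (10% lost at random). The sample size is not in dispute.

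**Illustration of selective loss.** The documents give no exclusion rates, so the shares below are assumptions. The calculation drops excluded patients and analyses the rest. It does not model the planned ITT analysis with imputation.

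*Pattern A: 25% of PHN-bound controls and 5% of everyone else lost.*
- Control: 127 × 0.348 = 44.2 cases, × 0.75 = 33.1; 82.8 non-cases × 0.95 = 78.7. Rate 33.1/111.8 = 29.6%.
- Intervention: 5% lost from both categories, 120.65 patients remain, rate still 16.3%.
- Relative risk 0.163/0.296 = 0.55, against 0.163/0.348 = 0.47 without loss.
- Power: pooled rate 0.227, null SE 0.0550, alternative SE 0.0547; (0.1335 − 1.960 × 0.0550)/0.0547 = 0.47, giving 68%.
- Overall loss (254 − 111.8 − 120.65)/254 = 8.5%, which is inside the 10% allowance.

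*Same pattern, no true effect (34.8% in both arms).* Observed 29.6% control v 34.8% intervention, relative risk 1.17. This is a spurious difference of about 5 points against the intervention. The chance of a significant result is about 13% against the intervention and about 0.2% in its favour.

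*Pattern B: 40% of PHN-bound intervention patients and 5% of everyone else lost.* Intervention: 20.7 × 0.60 = 12.4 cases; 106.3 × 0.95 = 101.0 non-cases. Rate 12.4/113.4 = 11.0% v 34.8%, relative risk 0.31, so the benefit is overstated.

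*Range when only PHN cases are lost (true relative risk 0.468):*

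| Cases lost, control / intervention | Observed rates | Relative risk | Power |
|---|---|---|---|
| 20% / 20% | 29.9% v 13.5% | 0.450 | 87.7% |
| 20% / 10% | 29.9% v 14.9% | 0.498 | 80.6% |
| 20% / 0% | 29.9% v 16.3% | 0.545 | 71.9% |
| 40% / 20% | 24.3% v 13.5% | 0.556 | 55.9% |

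The direction depends on which arm loses more poor-outcome patients.

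**The case against.** The strongest reply is that the Withdrawal criteria define no analysis set, whereas the Statistical analysis section does. Read together, a patient in breach leaves the per-protocol set, stays in ITT, and has missing values imputed. This largely stands. A reader might infer that criterion 3 removes patients from the ITT analysis, but the text does not say so. What remains is that the criterion is unrestricted and silent on continued follow-up, so the outcome may have to be imputed when it could have been observed.

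Second, a reader might infer that imputation cannot help. That goes too far. Table 1 records NRS-11 daily to day 7, then at day 14 and month 1, and arm is known. If exclusion follows recorded pain and arm, imputation that uses them could remove part of the bias, possibly much of it, and sensitivity analyses are planned. Nothing ensures that it removes all of it.

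Third, selective loss is inferred, and analgesia for persisting pain in both arms may reduce the motive for outside treatment. This stands as a limit on size, but the rule still applies.

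Fourth, a reader might extend the pain mechanism to criteria 1 and 2. The documents do not support that. Those items cover health changes that make continued participation unsuitable, and serious events that the team judges to require discontinuation; neither is triggered by pain.

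Finally, a reader might take the illustration as evidence of bias towards the new treatment. Pattern A works against the intervention and pattern B for it, and the documents do not say which, if either, would occur.

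**Conclusion.** The point holds as a conflict between an unrestricted exclusion rule and the stated aim of the ITT analysis. The consequence is that the primary outcome may go uncollected for patients who breach before month 3. This is stated text, not detail left to an analysis plan, and an analysis plan could not restore the missing scores.

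The size and direction of any bias are unknown. The figures (relative risk 0.55 instead of 0.47 and power 68% under pattern A; 29.6% v 34.8% when there is no effect) rest on assumed loss shares and a completer-only analysis. They show that selective loss within the 10% dropout allowance can matter, where random loss of 10% leaves power at 89.8%. They do not predict the result of the planned ITT analysis. That loss would be related to pain and arm is plausible, not demonstrated.

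**What to change.** In Withdrawal criteria, state that a criterion 3 breach determines only membership of the per-protocol set. Record the outside treatment, and continue the scheduled outcome assessments, with the month-3 NRS-11 as a minimum, unless consent is withdrawn. In Statistical analysis, declare ITT primary and state that it uses the outcomes observed after a breach, with imputation kept for values that are truly missing.

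For criteria 1 and 2, add only that outcome assessment continues where the patient consents. The clinical rules on discontinuation stay as they are.

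The cost is a few sentences of protocol wording and some follow-up effort at the month 3, 6 and 12 visits already in Table 1. The sample size does not change. The amendment is worth making before further outcomes are lost.

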### Recruitment

Trained researchers will determine eligible patients based on the inclusion and exclusion criteria mentioned above. If patients meet the eligibility criteria, researchers will explain the study’s purpose, interventions, potential benefits, possible risks, and countermeasures to the participants. Each subject will have at least 1 h to ask questions about the study and decide whether to participate. Then, subjects will sign a written informed consent form and have the right to withdraw from the study at any time. The confidentiality of participants' records will be protected. All participants will be asked to allow the research team to share relevant data. If participants withdraw from the study, they will also be asked if they consent to the use of their data.

